### 9.3 POPULATIONS FOR ANALYSES

All randomized participants will be included using an intent-to-treat analysis approach. Baseline differences at the patient level and within each clinic will be tested to determine if random assignment was successful. Any characteristics that differ between randomized groups will be included as covariates in all subsequent analytic models. If any significant imbalance is detected for any baseline characteristics, a sensitivity analysis will be performed, and the unbalanced characteristics will be incorporated into regression outcome models. We will evaluate the effectiveness of the tool across subgroups/categories by including a risk group classification variable in our models (to determine if there are differences in outcomes by group). If these risk groups are determined to confound the relationship between intervention and outcome, we will then stratify our analysis.

Additionally, if during the refinement and operationalization phase of Aim 1, specific high-risk groups are identified, and it is determined that there is a need to evaluate outcome by risk-group, for example, telemedicine versus in-person visit participants, we will add an additional block permutation and stratify randomization by telemedicine status in addition to clinic site.

### 9.4 STATISTICAL ANALYSES

*Leave blank. Text should be included under the relevant subheadings below.*

#### 9.4.1 GENERAL APPROACH

**Descriptive Statistics:** Categorical data will be presented as frequencies and percentages. Based on normality assessments, continuous data will be presented as means (standard deviations) or medians (interquartile range). Patient characteristics will be presented using descriptive statistics and compared between intervention and standard of care groups using two-sample t tests for continuous (normally distributed) variables and Pearson's chi-squared test will be used for binary and categorical variables.

**Inferential Tests:** The impact of the intervention will be assessed by comparing the outcome of interest between intervention and usual care groups using logistic or poisson regression (depending on distribution of outcome) and adjusting for identified covariates and assessing study intervention arm as the primary independent variable. A significant level (p-value) of 0.05 will be used with 95% confidence intervals reported. Two-tailed tests will be conducted unless there is a strong a priori basis for a one-tailed test.

**Covariates:** Covariates will be assessed individually between intervention and usual care groups and by outcome of interest. We will use Hosmer and Lemeshow's covariate inclusion approach (purposeful selection at each modeling step) when developing models to ensure inclusion of biologically and statistically relevant variables.

**Assumptions:** Data will be checked for normality of distribution prior to analysis. If assumptions are violated, appropriate transformations will be applied, or non-parametric tests will be used.

#### 9.4.2 ANALYSIS OF THE PRIMARY EFFICACY ENDPOINT(S)

**Primary Endpoint: Increase in Retinal screening completion (H2.1)**

**Measurement:** Boolean variable (Yes/No) indicating completion of retinal screen within the defined study period (60 days from randomization).

**Scale:** Binary

**Analysis:** Chi-squared test or logistic regression will be used to compare screening completion rates between intervention and usual care groups. Regression covariates may include demographics and baseline clinical factors. Covariate selection will aim for a parsimonious model to achieve clarity and avoid overfitting. We will evaluate the intervention effectiveness across subgroups/categories by including a risk group classification variable in our models (to determine if there are differences in outcomes by group). If these risk groups are determined to confound the relationship between intervention and outcome, we will then stratify our analysis.

**Results Presentation:** Adjusted odds ratios with 95% confidence intervals will be reported.

**Assumption Checks:** When logistic regression is used, the data will be assessed for linearity, absence of multicollinearity, and influential outliers.

**Populations:** All enrolled participants will be included in the analysis.

**Missing Data:** Multiple deletion or imputation methods will be used to handle missing data depending on the pattern of missingness, e.g. if entire surveys are missing if missingness is driven by specific items or response groups in the survey, and/or if the data is missing completely at random. We have allowed for a 10% dropout/withdrawal rate between enrollment and intervention, and thus can use pairwise or listwise deletion of up to 10% of participants and still maintain adequate power for analysis.

**Outliers/Non-adherence:** Data outliers will be assessed to ensure they are not the result of data entry or measurement error. True data outliers will be handled either by trimming, adjusting the weight of the outliers, or by using robust regression techniques. Non-adherence will be addressed by analyzing data per-protocol in addition to intent to treat.

---

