The primary analysis will compare diabetic retinopathy screening completion between the intervention group and the standard of care group. Logistic regression will be used to estimate intervention efficacy using treatment arm as the main exposure variable and the odds ratio (OR) including 95 % CI will be presented. Hosmer and Lemeshow's approach to purposeful selection of variables will be used for final model selection.

Secondary analysis will compare diabetic retinopathy screening results between treatment arms using the same logistic regression approach as the primary analysis. Missing treatment results will be classified in this analysis and no diagnosis.

**Exploratory analysis:** Exploratory analyses will be performed to assess relationships between screening completion, screening outcomes, social determinates of health, and clinical risk factors. Changes in patient education/knowledge outcomes will be assessed using difference in

differences analysis. These analyses will be used to identify items that are most strongly related to barriers and/or compliance, and be used to refine and guide future implementation strategies.

Additionally, where both EyeArt and ICD-10 codes are available, results will be compared and shared with EyeArt, however these results will not be generalizable as only results from participants in the intervention group who received ungradable or abnormal EyeArt results and who were examined by an eye specialist and had results returned to the SYH will be available for comparison.

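### Protocol 9.4.2 and 9.4.3 allow genuine observations to be trimmed or down-weighted under an undefined outlier rule, which conflicts with intent-to-treat and can distort the odds ratio if outliers are found from model residuals

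*Combined protocol and SAP*

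**What the plan says.** Protocol 9.4.2 covers the primary endpoint, a yes/no variable for screening completion. Under Outliers/Non-adherence it begins with a data check: "Data outliers will be assessed to ensure they are not the result of data entry or measurement error". It then turns to what survives the check: "True data outliers will be handled either by trimming, adjusting the weight of the outliers, or by using robust regression techniques". Section 9.4.3 repeats both sentences for DR diagnosis, which is categorical. Neither section defines an outlier, sets a threshold, chooses among the three options or confines them to a sensitivity analysis.

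Under Assumption Checks, 9.4.2 adds: "When logistic regression is used, the data will be assessed for linearity, absence of multicollinearity, and influential outliers".

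On who is analysed, protocol 9.3 says "All randomized participants will be included using an intent-to-treat analysis approach". The Populations paragraph of 9.4.2 takes in everyone enrolled, and the SAP (Analysis Populations) makes ITT primary.

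On method, the protocol says "Chi-squared test or logistic regression will be used to compare screening completion rates between intervention and usual care groups", while the SAP says "Logistic regression will be used to estimate intervention efficacy using treatment arm as the main exposure variable". The SAP has no outlier rule and does not withdraw the protocol's. Its Blinding paragraph states that the data analysts are unblinded.

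**The concern.** The rule acts on values already confirmed as genuine. Trimming them removes valid randomised participants once outcomes are known; down-weighting reduces what they contribute. Either way the analysis no longer treats everyone randomised equally, and the choice of rule, cut-off and option is left to analysts who can see arm and outcome.

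A binary outcome has no extreme values of its own, but a logistic model does produce outliers: people whose yes/no result disagrees with their fitted probability. The check for influential outliers in the same section allows them to be identified that way. Removing people because the model predicted them poorly makes the remaining data agree with the model more than they should. At stake are the size of the reported odds ratio and the 5% error rate of the primary test.

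**Working it through.** **1. The plan's own figure.** Inputs from the SAP sample-size section: 59% versus 69%, two-sided alpha 0.05, power 80%, Pearson chi-squared. With mean rate 0.64,

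n per arm = [1.960 × √(2 × 0.64 × 0.36) + 0.842 × √(0.59 × 0.41 + 0.69 × 0.31)]² / 0.10² = 360.5, rounded up to 361.

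The total of 722 reproduces. The odds ratio is (0.69/0.31)/(0.59/0.41) = 1.55.

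**2. Arm-only model, primary endpoint.** The largest Pearson residual in an arm with completion p above one half belongs to a non-completer and equals √(p/(1−p)). At 59% it is √(0.59/0.41) = 1.20; at 69% it is √(0.69/0.31) = 1.49. A cut-off of 2 removes nobody at the design rates. It would begin to flag every non-completer in an arm only once p/(1−p) exceeds 4, that is, completion above 80%.

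**3. Model with a covariate, primary endpoint.** Simulation with 361 per arm and a logistic model with arm and one standard-normal covariate. Flagged participants are removed or down-weighted, the model is refitted and the usual Wald test applied. The covariate slope (log-odds per SD) and the outlier rules are assumptions, because the documents give neither.

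Two-sided false-positive rate, 59% in both arms (2,000 trials each; Monte Carlo error about 1 point near 5%):

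| Rule | slope 0 | slope 0.5 | slope 1.0 |
|---|---|---|---|
| None, all kept | 5.4% | 4.7% | 5.1% |
| Residual above 2 in absolute value | 5.4% | 7.4% | 14.5% |
| Residual above 2.5 | 5.4% | 5.0% | 8.3% |
| Cook's distance above 4/n | 6.5% | 8.5% | 12.0% |
| Huber-type weights (1.345) | 5.9% | 8.1% | 10.2% |
| Covariate beyond 2 SD | 5.4% | 4.6% | 4.9% |

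Repeat runs for the cut-off of 2 gave 6.6% and 6.8% at slope 0.5, and about 12.5% and 13% at slope 1.0.

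Median odds ratio, 59% versus 69% (1,000 trials each; true conditional values 1.55, 1.58, 1.69):

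| Rule | slope 0 | slope 0.5 | slope 1.0 |
|---|---|---|---|
| None, all kept | 1.54 | 1.58 | 1.69 |
| Residual above 2 | 1.54 | 1.75 | 2.11 |
| Residual above 2.5 | 1.54 | 1.61 | 1.85 |
| Cook's distance above 4/n | 1.61 | 1.70 | 1.98 |
| Huber-type weights | 1.71 | 1.77 | 1.95 |
| Covariate beyond 2 SD | 1.54 | 1.58 | 1.70 |

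In these 59% versus 69% runs the cut-off of 2 removed 0%, 1.5% and 3.7% of participants; the covariate rule removed about 4.6%.

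**4. Direction and precision.** With equal rates the median odds ratio stayed at 1.00 under every residual or influence rule in the table: single estimates are pushed away from 1 both ways. Standard errors do not shrink. At slope 1.0 with cut-off 2, the mean standard error of the arm coefficient rises from 0.167 to 0.178 with no effect and from 0.172 to 0.191 at 59% versus 69%. The error rate rises because the estimates spread by more than the standard error allows for.

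**5. Secondary endpoint.** The SAP applies the same logistic approach and counts missing results as no diagnosis. Taking its 11% diagnosed among those screened for both arms, the diagnosed proportions are 0.11 × 0.59 = 6.5% and 0.11 × 0.69 = 7.6%. A diagnosed participant's arm-only residual is √(0.935/0.065) = 3.8 or √(0.924/0.076) = 3.5. Cut-offs of 2, 2.5 or 3 would each flag every diagnosed participant, the very events being compared. No covariate assumption is needed here.

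**The case against.** A reader might infer that the plan will remove participants with unexpected outcomes and so inflate the odds ratio and the error rate. The documents do not support that as a certainty.

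- The outlier sentence follows a check for entry and measurement error, which reads most naturally as being about data values such as clinical covariates. The check for influential outliers is in a separate paragraph and orders assessment, not removal. If outliers are extreme covariate values, the simulation shows no inflation, only lost participants.
- An arm-only model with cut-off 2 at the design rates removes nobody.
- The chi-squared test that 9.4.2 also permits has no residual step, and robust regression need not drop anyone.
- The SAP's primary analysis contains no outlier rule, and it handles distributional problems by diagnosis, transformation and non-parametric tests.
- Two further inferences, that the rule biases the odds ratio upward when there is no effect and that it shrinks standard errors, are contradicted by step 4.

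All of this stands, and it limits the claim about size. It does not remove the conflict with the analysis population, which follows from trimming under any definition of an outlier. Nor does the SAP's silence settle the matter, since it neither adopts nor cancels the protocol's sentence. Robust fitting is not automatically harmless either: Huber-type weights moved both the error rate and the odds ratio.

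**Conclusion.** The point holds as an undefined rule, ill suited to binary or categorical endpoints, that contradicts the stated analysis population if trimming is used and leaves an open choice to unblinded analysts. The numerical harm is conditional on finding outliers by residual or influence. On that reading, with a cut-off of 2, the false-positive rate runs from about 5% (no prognostic covariate) through about 7% (log-odds 0.5 per SD) to about 13 to 14% (log-odds 1.0). The median odds ratio at 59% versus 69% is unchanged, or goes from 1.58 to about 1.73, or from 1.69 to about 2.1. A cut-off of 2.5 gives about 5 to 8%. Covariate strength and cut-off are assumptions, and the range includes no effect. For the secondary endpoint the usual cut-offs would flag every diagnosed participant; this rests on the 11% applying in both arms and on an arm-only model.

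**What to change.** Delete the sentence on true outliers from protocol 9.4.2 and 9.4.3. In its place state that verified data errors are corrected, that every randomised participant is kept at full weight in the primary and secondary analyses, and that influential observations are examined in a sensitivity analysis only.

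The cost is protocol wording. The analysis sample size stays at 722 (361 per arm), and no data collection changes.

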#### 9.4.3 ANALYSIS OF THE SECONDARY ENDPOINT(S)

**Secondary Endpoint 1:** Early-stage DR diagnosis and treatment (H2.2)

**Measurement:** Diagnosis of DR.

**Scale:** Categorical (vtDR and mtmDR positive, vtDR negative and mtmDR positive, vtDR and mtmDR negative, ungradable).

**Analysis:** Chi-squared test or logistic regression will be used to compare screening completion rates between intervention and usual care groups. Regression covariates may include demographics and baseline clinical factors. Covariate selection will aim for a parsimonious model to achieve clarity and avoid overfitting. We will evaluate the intervention effectiveness across subgroups/categories by including a risk group classification variable in our models (to determine if there are differences in outcomes by group). If these risk groups are determined to confound the relationship between intervention and outcome, we will then stratify our analysis.

**Results Presentation:** Adjusted odds ratios with 95% confidence intervals will be reported.

**Assumption Checks:** When logistic regression is used, the data will be assessed for linearity, absence of multicollinearity, and influential outliers.

**Populations:** All enrolled participants will be included in the analysis.

**Missing Data:** Multiple deletion or imputation methods will be used to handle missing data depending on the pattern of missingness, e.g. if entire surveys are missing if missingness is driven by specific items or response groups in the survey, and/or if the data is missing completely at random. We have allowed for a 10% dropout/withdrawal rate between enrollment and intervention, and thus can use pairwise or listwise deletion of up to 10% of participants and still maintain adequate power for analysis.

**Outliers/Non-adherence:** Data outliers will be assessed to ensure they are not the result of data entry or measurement error. True data outliers will be handled either by trimming, adjusting the weight of the outliers, or by using robust regression techniques. Non-adherence will be addressed by analyzing data per-protocol in addition to intent to treat.

**Exploratory Endpoints:** Knowledge, Attitudes, Self-efficacy, and Patient Satisfaction (H2.3)

**Measurement:** Outcomes representing participant knowledge, attitudes, self-efficacy, and satisfaction with study participation.

**Scale:** Multiple outcomes will be explored and may include nominal, binary, or categorical data.

**Analysis:** We will explore the association between various demographic and clinical characteristics and knowledge, attitudes, self-efficacy, and patient satisfaction. Given the exploratory nature of this endpoint, analysis will be used to refine intervention implementation methods, identify barriers to participation, and increase participant satisfaction.

---

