**Secondary outcomes**

- Diabetic retinopathy diagnosis as determined by EyeArt or ophthalmologist
  - EyeArt-System results: normal, mtmDR, vtDR, or ungradable
  - Eye specialist referral clinical classification, using ICD-10 codes: E10.9, E11.9, E10.329, E11.329; E10.339, E11.339; E10.321, E11.321, E10.331, E11.331, E10.349, E11.349, E10.341, E11.341, E10.359, E11.359, E10.351, E11.351.
- Completion of retinal screen (AI-DRS-System or screening by an ophthalmologist) within 6 months of enrollment

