**AI Algorithm and Performance:** The EyeArt AI system (EyeArt) has a clinically aligned framework and is trained on 375,000 images and validated on over 250,000 images. The system requires a digital fundus camera to capture two 45° field of view images, one centered on the optic disc and one centered on the macula. These images may be taken without dilation. EyeArt has been validated in a prospective, multicenter, pivotal clinical trial including 942 individuals with DM, where EyeArt demonstrated high accuracy against the Early Treatment Diabetic Retinopathy Study (ETDRS) reference standard clinical reference standard (mtmDR sensitivity: 96%, specificity: 88%, and vtDR sensitivity: 97%, specificity: 90%) by providing conclusive reports for >97% of eyes with reference standard while not requiring dilation for most. In a retrospective study of more than 100,000 consecutive encounters with people with DM, EyeArt also achieved a performance of 91.3% sensitivity and 91.1% specificity in detecting mtmDR. A subgroup analysis of participants in this clinical trial demonstrated that the sensitivity against the ETDRS reference standard for detection of mtmDR was significantly greater with EyeArt than with either an ophthalmologist dilated examination. Therefore, the FDA-cleared EyeArt is suitable for the prospective evaluation proposed in this application. The AI algorithms in EyeArt will be static (fixed) during the proposed evaluation process and will not be retrained. Therefore, no data requirements are associated with retraining the AI algorithms in EyeArt. Based on the existing EyeArt AI algorithm outcomes, SYHealth will implement a patient-centered model for its population of focus. In all four outcomes (mtmDR positive, vtDR positive), (mtmDR positive, vtDR negative), (mtmDR negative, vtDR negative), and ungradable, SYHealth's model will integrate a trained SYHealth clinical staff that will ensure patient care to proper follow up based on the EyeArt AI system results and as indicated by the primary care

provider. Preliminary Studies that guide the proposed AI System for autonomous DR screening are listed in **Appendix 3**.

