| Evaluate the implementation and effectiveness of a multicomponent AI clinical intervention on DR screenings, early stages of DR detection, and referrals to the specialist for follow up on abnormal results. | 
 
1. Completion of DR screening. Data will be obtained through EHR at the time of the enrollment (baseline).
 
2. Results of the DR screening: for usual care specific diagnosis; for intervention group defined as normal, mild-to-moderate DR (mtmDR), visual threatening DR (vtDR) or ungradable. Data will be obtained through EHR at the time of the enrollment (baseline) and over the duration of the study.
 
3. Referral to specialist completion status and final diagnosis. Data will be obtained through EHR over the duration of the study.
 
 | 
To evaluate the effectiveness of the clinical intervention will be tested using a RCT (Aim 2), with the “intervention group”, which is characterized by 1) conducting autonomous DR screening system (H2.1) with 2) integration of the results into the EHR (H2.2). The “usual care” group represents the existing primary care model, which involves medical visits, referral to the specialist for a DR screening, and follow-up.
 
In addition, to evaluating the impact and efficiency of the POC-AI System we will also collect AI system data, number of orders submitted, screenings completed (images), number of ungradable and time of attempts, time the patient spent in front of the camera.
 |

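### Protocol 9.4.3 analyses screening completion under the DR diagnosis endpoint, and neither document defines a DR event common to both arms

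*Combined protocol and SAP*

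**What the plan says.** Protocol 9.4.3 describes Secondary Endpoint 1 in three lines that do not fit together:

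- The variable: "Measurement: Diagnosis of DR".
- Its scale: "Categorical (vtDR and mtmDR positive, vtDR negative and mtmDR positive, vtDR and mtmDR negative, ungradable".
- Its analysis: "Chi-squared test or logistic regression will be used to compare screening completion rates between intervention and usual care groups". Adjusted odds ratios with 95% confidence intervals are then promised.

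Protocol section 3 records results differently by arm: "for usual care specific diagnosis; for intervention group defined as normal, mild-to-moderate DR (mtmDR), visual threatening DR (vtDR) or ungradable".

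The SAP, under Secondary outcomes, defines the endpoint as "Diabetic retinopathy diagnosis as determined by EyeArt or ophthalmologist". It lists the EyeArt results and 18 ICD-10 codes for the specialist's classification. Under Statistical Methods it says: "Secondary analysis will compare diabetic retinopathy screening results between treatment arms using the same logistic regression approach as the primary analysis". The sentence after that is garbled but evidently means that missing results count as no diagnosis.

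**The concern.** Section 9.4.3 is the protocol's operative analysis text for the only secondary endpoint with a formal hypothesis in 9.1. Followed to the letter, it would report the primary outcome a second time under the heading of DR diagnosis.

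An analyst who sees the slip and turns to DR diagnosis still has to invent the outcome. Someone must decide which EyeArt categories and which ICD-10 codes mean DR, what to do with ungradable images, and whether an EyeArt positive counts before a specialist confirms it. The SAP states that study staff and data analysts are unblinded, so these choices could be made with the arm-level results in view.

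**Working it through.** **1. Which outcome is compared, place by place**

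| Place | Outcome compared between arms |
|---|---|
| Protocol 9.4.2, Analysis (primary) | Screening completion |
| Protocol 9.4.3, Analysis (secondary) | Screening completion; same sentence as 9.4.2 |
| Protocol 9.4.3, Measurement | DR diagnosis |
| Protocol 9.1, secondary hypotheses | DR diagnosis |
| Protocol 8.1 | Both primary and secondary outcomes |
| Protocol 9.4.1 | The outcome of interest, by regression |
| Protocol 9.4.7 | A separate DR diagnosis model is named |
| SAP, Statistical Methods | DR screening results |

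The Analysis line of 9.4.3 stands alone against the rest. The likely cause is text carried over from 9.4.2.

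**2. Can the scale serve both arms?**

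The four levels are EyeArt's result set. Protocol 2.2 lists them as such: "In all four outcomes (mtmDR positive, vtDR positive), (mtmDR positive, vtDR negative), (mtmDR negative, vtDR negative), and ungradable". Usual care yields a specific diagnosis (section 3) or an ICD-10 code (SAP), and no mapping to the four levels is given. The threshold is also unsettled. Section 3 expands mtmDR as mild-to-moderate, section 8.1 as more than mild, and section 2.2 says dilated exams stage mild disease too.

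**3. Is a binary event defined anywhere?**

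No.

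- Section 9.1 gives hypotheses only, 8.1 and 9.4.1 name tests, and 9.4.7 names a model.
- The SAP covers missing results, but ungradable is a listed result and not clearly a missing one.
- The SAP's code list is not divided into codes that count as DR and codes that do not.
- The SAP accepts a diagnosis by EyeArt, while protocol 2.3.3 and 8.1 say the AI result is not the final diagnosis.

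**4. How large is the effect against which these choices matter?**

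Inputs (SAP sample size section; protocol 9.2): completion 59% and 69%; DR diagnosed in 11% of those screened.

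- The plan's own figure is a 16% increase in DR diagnosis. Check: 0.69/0.59 − 1 = 16.9%, close to the stated value if it is read as relative.
- Usual care: 0.59 × 0.11 = 6.49% of all randomised.
- Intervention: 0.69 × 0.11 = 7.59% of all randomised.
- Difference: 1.10 points. In participants, 0.011 × 361 = 4.0 or 0.011 × 424 = 4.7 per arm.
- Two-sided power at α = 0.05 is about 8.3% with 361 per arm and 9.1% with 424 per arm. About 16,980 participants in total would give 80%.

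The planned 722 (361 per arm) reproduces exactly, but it concerns completion and has no bearing here.

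**5. How much could the event definition move the intervention arm?**

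The documents give no figure for this trial, so everything in this step is an assumption.

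- *Break-even:* 1.10/0.69 = 1.6. If 1.6% of screened intervention participants have a result that could be counted either way, the choice moves that arm by as much as the expected effect.
- *Ungradable:* section 2.2 reports conclusive results for more than 97% of eyes in an outside trial. Applied to people, 0% to 3% ungradable gives 0 to 0.69 × 3% = 2.1 points of all randomised.
- *Unconfirmed EyeArt positives:* take 11% as the true rate in those screened and apply section 2.2's mtmDR accuracy per participant. With 96% sensitivity and 88% specificity: 0.69 × (0.11 × 0.96 + 0.89 × 0.12) = 14.7%. With 91.3% and 91.1%: 0.69 × (0.11 × 0.913 + 0.89 × 0.089) = 12.4%. Either compares with 7.6% for true DR.

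**The case against.** A reader might infer from 9.4.3 that DR diagnosis is never compared and the secondary hypothesis goes untested. The documents do not support that. Protocol 8.1, 9.1, 9.4.1 and 9.4.7 and the SAP all provide for the comparison, and one sentence should not be read against all of them.

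A reader might also infer that completion is to be tested on a four-level scale. That is not so either: the Scale line follows the Measurement line and describes the diagnosis variable.

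Two further points count for the plan. First, 9.4.3 names a chi-squared test as well as logistic regression, and a chi-squared test accepts four levels. That stands as a point of method, but both arms must populate the same four levels, and only the intervention arm does; the promised odds ratio also needs a binary outcome. Second, the SAP goes part of the way: it gives usual care its own source of diagnosis and counts missing results as no diagnosis, which suggests a yes/no outcome among all randomised. That stands too. It leaves open what counts as yes.

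The ungradable figure is weak evidence. It is per eye, comes from another trial in which some eyes were dilated (here EyeArt participants are not), and moves the result only if ungradable is counted as DR, which neither document proposes.

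**Conclusion.** The point holds in two parts. First, the Analysis sentence of 9.4.3 names the wrong outcome and contradicts its own section, 9.1, 9.4.7 and the SAP. Taken alone, that is a wording error whose intent can be recovered. Second, and of more consequence, no DR event common to both arms is defined: the scale is EyeArt's alone, usual-care diagnoses are not mapped to it, and the yes behind the odds ratio is not stated.

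The primary analysis is unaffected. For the secondary endpoint the expected contrast is about 1.1 points (6.5% against 7.6%), so the definition can matter as much as the effect. The contrast assumes the same 11% yield among those screened in both arms and counts non-completers as no diagnosis. The figures for ungradable and unconfirmed positive results are illustrations under stated assumptions, not estimates for this trial. This should be corrected before analysis.

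**What to change.** 1. In protocol 9.4.3, replace the Analysis sentence with: *Logistic regression will compare the proportion of all randomised participants diagnosed with DR (yes/no) between the two arms.*
2. In both 9.4.3 and the SAP, define that event once for both arms. State which EyeArt categories and which of the listed ICD-10 codes count as DR, and whether an EyeArt positive without specialist confirmation counts. Use one meaning of mtmDR throughout.
3. Count negative, unscreened, and ungradable without a later diagnosis as no. This follows the SAP's rule for missing results; repair the wording of that rule at the same time.
4. Report the four EyeArt categories descriptively, in the intervention arm only.

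The cost is a few sentences in each document, with no change to conduct, data collection or sample size. The change makes the comparison well defined but does not give it adequate power, so the report should lead with the estimate and its interval.
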